### Design considerations

For comparison we have chosen to use a wait-list control. This will enable us to compare the intervention to treatment as usual, with the option for those in the control group to receive group music therapy at the study end.

We propose offering three sessions per week to participants for a number of reasons. First, in a previous study in a similar environment [37] there were high rates of attrition in the once-per-week group. Our previous research within an acute inpatient environment demonstrated that offering an increased frequency was acceptable, of therapeutic benefit and increased the chances of attending a greater number of music therapy sessions [53]. Second, given the potential difficulties in motivation and attending sessions, the increased frequency may help to build momentum and keep attendance going. Greater frequency also means it may be possible to develop a greater stability of group membership, which will help to foster trust and commitment in the group and, in the case of ongoing songwriting and performance work, provide opportunities to progress these longer-term activities. In total, 42 sessions are available to participants, which may enable us to detect a large effect on depressive symptoms, and medium-to-large effects on general symptoms [34].

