### Randomisation

Randomisation will occur once all 30 participants have been recruited and baseline measures have been completed. In order to obtain sufficient data on the intervention, we will utilise simple block randomisation with unbalanced allocation so that 20 participants receive the intervention and 10 are allocated to the wait-list control group. A researcher independent of the study team will perform the randomisation using the Experimental Design Generator and Randomiser (EDGAR-II) [65] and inform the music therapists and unblinded member of the study team of the allocation by email. The music therapists will then inform participants of their allocation and provide additional support if required.

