Researcher time and costs per participant	Researcher diary	N/A	Researcher time exceeds allocated time requiring additional study support	Researcher time and cost only just covers time required	Researcher time and cost fully covers time required	6 months post-intervention
Appropriate outcome measures	Variability of outcome Estimate of control mean and SD of change	No difference or clinically important difference favouring control detected based on confidence limits	Difference cannot be detected based on confidence limits but data suggest improvement favouring intervention	Difference can be detected based on confidence limits	Clinically important difference can be detected based on confidence limits	End of intervention
Intervention components	Therapist adherence	Adherence <50%	Adherence <50%	Adherence 50–75%	Adherence >75%	End of intervention
	End interviews	Serious concerns expressed regarding intervention	Major suggestions to adapt intervention	Minor suggestions to adapt intervention	No concerns or suggestions to adapt intervention	
Intervention adherence	Therapist self-rated adherence Video-rated adherence	Adherence <25%	Adherence 25–50%	Adherence 50–75%	Adherence >75%	End of intervention
Estimate of cost of intervention and services received	Therapist time CSRI	Cost significantly greater than usual care, no potential to modify intervention, no indication of benefits	Cost is greater than usual care - intervention may be modified, but outcomes suggest some benefits	Cost is greater than usual care but outcomes strongly suggest benefits	Cost is equivalent to or slightly greater than usual care, outcomes strongly suggest benefits	6 months post-intervention

*HCPs* healthcare professionals, *N/A* not applicable, *CSRI* Client Services Receipt Inventory

Observer rated:Symptoms of depression as measured by the Montgomery-Åsberg Depression Rating Scale (MADRS) [62, 66, 67]Social functioning as measured by the life skills profile (LSP) [68]Level of hospitalisation as measured by admission, length of stay and number of readmissions

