### Statistical analysis

#### Feasibility

As this is a feasibility study, the main statistical reporting will comprise descriptive statistics and calculation of effect sizes. We will assess:• Acceptability of methodology to professionals and patients through interviews via recruitment rates, compliance, end interviews      • Feasibility of recruitment processes• Deviation around specific post-intervention, and 3-month and 6 month post-intervention follow-up assessment dates for actual data collection• Number of eligible participants, participation rates and retention rates• Researcher time and costs per participant• Appropriateness of outcome measures

Descriptive analyses will establish recruitment and drop-out rates and the distribution of baseline characteristics and all outcomes post-intervention, and 3 months and 6 months post-intervention. The research team will reflect upon the representativeness of the demographics in terms of the general population of patients that could potentially be useful in assessing the intervention.

Recruitment and drop-out rates will be monitored on a monthly basis allowing for examination and reporting of patterns and whether there are any obvious trends. This may inform the choice of the primary outcome for a full-scale trial allowing for drop-outs in a sample-size calculation.

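### Table 1 judges whether the outcome measures are suitable by whether a 20 v 10 comparison detects a treatment effect, so sound measures can often miss the 'continue without modification' bands

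*Protocol article*

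**What the plan says.** Table 1, under Outcome measures and endpoints, lists feasibility outcomes with four graded bands running from Stop to Continue without modifications. For appropriate outcome measures, assessed at the end of the intervention, the method is "Variability of outcome Estimate of control mean and SD of change". The bands are:

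- Stop: "No difference or clinically important difference favouring control detected based on confidence limits".
- Continue, modify protocol: "Difference cannot be detected based on confidence limits but data suggest improvement favouring intervention".
- Continue but monitor closely: a difference is detectable on the confidence limits.
- Continue without modifications: "Clinically important difference can be detected based on confidence limits".

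Under Randomisation, "20 participants receive the intervention and 10 are allocated to the wait-list control group". Under Statistical analysis, the Feasibility part says that "the main statistical reporting will comprise descriptive statistics and calculation of effect sizes". The Clinical outcomes part plans linear regression adjusted for the baseline score. It uses the confidence limits to ask whether a clinically important difference is ruled out, where such a difference is known. The article states no effect size, clinically important difference or confidence level for the Table 1 row, and does not say how the rows combine.

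**The concern.** The row sets out to judge the measures and then grades the therapy. A scale can be well completed, free of floor and ceiling effects and usefully variable while a 30-patient comparison still gives an interval that includes zero. Conversely, a chance-large effect would earn the top band for a measure with poor completion. The row therefore cannot answer the objective it serves in Aims and objectives: appropriateness of the measures, variability for a sample size calculation, and the control mean.

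Two further problems follow.

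- The test in Table 1 (is a difference detected?) is not the test in Clinical outcomes (is an important difference ruled out?). A wide interval can fail the first while ruling out nothing under the second.
- The Stop and Modify cells both describe a difference that is not detected. Only the added clause about a favourable trend separates them.

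At stake is a misleading entry in the table of success criteria, which is a main product of a feasibility trial.

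**Working it through.** **Inputs from the article.** 20 v 10 patients (Randomisation); baseline-adjusted linear regression (Clinical outcomes); assessment at end of intervention (Table 1); best attrition band below 30% (Table 1), whose edge leaves 14 v 7.

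**Assumptions, because the article gives no values.** Two-sided 95% limits, the level used in Sample size for the participation rate; true effect d = 0.5 or 0.8 SD; baseline–outcome correlation r = 0, 0.5 or 0.7.

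**Step 1: the article's own precision figure.** With n = 30 and a rate of 25%, 1.96 × √(0.25 × 0.75/30) = 15.5%, which agrees with the stated ±15% to rounding. It concerns participation. No precision is stated for the treatment effect that the row uses.

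**Step 2: width of the interval for the effect.** SE = √[(1 − r²)(1/20 + 1/10)] SD, which is 0.387, 0.335 and 0.277 for r = 0, 0.5 and 0.7. The t quantile is 2.048 (28 df, unadjusted) or 2.052 (27 df, adjusted). The half-widths are 0.79, 0.69 and 0.57 SD.

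**Step 3: chance of missing both 'continue without modification' bands.** This is the probability that the interval does not exclude zero in favour of therapy: F(t quantile; df, d/SE), with F the noncentral t distribution function.

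**Step 4: chance of Stop if Stop means an estimate at or below zero.** This is Φ(−d/SE).

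Worked case, d = 0.5 and r = 0.5: d/SE = 0.5/0.335 = 1.49. The chance of detection is 30%, so 70% miss. Φ(−1.49) is about 7%.

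| Arms | True d | Miss both bands (r = 0 / 0.5 / 0.7) | Estimate ≤ 0 (r = 0 / 0.5 / 0.7) |
|---|---|---|---|
| 20 v 10 | 0.5 | 76 / 70 / 59% | 10 / 7 / 4% |
| 20 v 10 | 0.8 | 49 / 37 / 20% | 2 / 1 / 0.2% |
| 20 v 10 | 1.0 | 30 / 18 / 6% | below 1% |
| 14 v 7 | 0.5 | 82 / 78 / 70% | 14 / 11 / 7% |
| 14 v 7 | 0.8 | 63 / 53 / 37% | 4 / 2 / 1% |

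A simulation of the adjusted analysis (20,000 runs, 20 v 10, r = 0.5) gave 71% missing at d = 0.5 and 38% at d = 0.8, in agreement. Clustering within the therapy groups, with an assumed intra-cluster correlation of 0.05 to 0.10 and r = 0.5, raises these to 73–76% and 43–48%.

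**Step 5: Table 1 beside Clinical outcomes.** Suppose r = 0.5 and, for illustration only, a clinically important difference of 0.5 SD.

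- An estimate of 0.40 SD gives 0.40 ± 0.69, or −0.29 to 1.09. Table 1 says modify. Clinical outcomes says an important benefit is not ruled out.
- An estimate of −0.05 SD gives −0.74 to 0.64. Table 1, read by sign, says Stop. Clinical outcomes again says an important benefit is not ruled out.

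**The case against.** **The middle band is a Continue band.** In a study meant to refine its intervention and design, 'Continue, modify protocol' is an ordinary result. This stands. A reader might infer that an effective therapy would often be stopped, and the figures do not support that on the natural reading. The Modify cell claims results that favour the intervention, which leaves Stop with estimates at or below zero: 4–10% at 0.5 SD and at most 2% at 0.8 SD with full retention. Stop reaches the 59–76% range at 0.5 SD only if it takes in every interval that includes zero, and that reading leaves the Modify cell empty.

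**The effect size is the reviewer's choice.** True. The article expects a large effect on depressive symptoms, so 0.8 SD may be the fairer case. At 1.0 SD with strong baseline correlation and full retention the miss rate falls to 6%.

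**The analysis is not purely descriptive.** Also true. The sentence on descriptive reporting includes effect sizes, and Clinical outcomes openly plans a between-arm regression. The real mismatch is with the ruled-out test there.

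**Other stronger inferences fail.** No text makes this row decisive for a full trial; it is one of many. The remark in Design considerations, "which may enable us to detect a large effect on depressive symptoms", is a hedged argument about the number of sessions and not a power claim. The cost row's Stop cell, "Cost significantly greater than usual care, no potential to modify intervention, no indication of benefits", needs three conditions together at 6 months, and Clinical outcomes already calls the economic work descriptive.

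None of this answers the main point: the cells do not use the quantities that the row names.

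**Conclusion.** The point holds in limited form and should be fixed. Without any assumption about effect size, the row's cells do not measure its stated outcome, they apply a different test from Clinical outcomes, and the wording of Stop and Modify is not cleanly separated.

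The probabilities show that the mismatch has practical consequences. They rest on assumed effect sizes, baseline correlations and a 95% level. With full retention and no clustering, an effective therapy misses both 'continue without modification' bands in 59–76% of trials at 0.5 SD and 20–49% at 0.8 SD, with nothing wrong with the measures. Attrition or clustering raises these figures. The usual consequence is an unwarranted 'modify' entry rather than a wrong Stop, and the article does not say that this row alone settles whether a full trial follows.

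**What to change.** Replace the four cells with criteria on the measures themselves: completion at the post-intervention visit, floor and ceiling effects, and the SD of the outcome with its confidence interval, with bands set in advance. Report the treatment effect and its interval descriptively, and state that an interval including zero neither stops nor modifies the programme.

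If an effect-based criterion is kept, align it with Clinical outcomes: it should apply only when the interval rules out a clinically important benefit or shows a clinically important difference favouring control. State the clinically important difference and the confidence level. With two-sided 95% limits, the chance of wrongly stopping a therapy whose true benefit is at least that difference is then at most 2.5%. Such a criterion would seldom apply at this size: for an illustrative difference of 0.5 SD and r = 0.5, the estimate would have to fall below 0.5 − 0.69 = −0.19 SD.

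The cost is rewording one table row and choosing its thresholds. No extra patients, visits or data are needed.

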### Outcome measures and endpoints

Our primary interest is in the feasibility of the trial design and intervention. A summary of the main feasibility outcomes, success criteria and timing is shown in Table 1. Proposed clinical outcomes are:

**Table 1 Tab1:** Methods and timing for assessing, recording and analysing outcome parameters

Outcome	Method	Success criteria				Timing
		Stop	Continue, modify protocol	Continue without modification but monitor closely	Continue without modifications	
Acceptability of methodology	Recruitment and retention rates as below					End of recruitment (week 8)
	Compliance	Mean attendance <10 sessions	Mean attendance <14 sessions	Mean attendance 14 sessions	Mean attendance 14+ sessions	End of intervention (week 22)
	End interviews	Unfavourable views, serious concerns	Unfavourable views, suggestions for modification	Favourable views, suggestions for modification	Favourable views, no concerns	1 month post-intervention (week 26)
Feasibility of recruitment processes	Screening rates	Identify <50 potentially eligible subjects	Identify <100 potentially eligible subjects	Identify 100–128 potentially eligible subjects	Identify >128 potentially eligible subjects	End of recruitment
	Recruitment rates	Recruit <50% of sample size	N <25 in 8wks, <5% per week	*N* = 25–30 in 8wks, <13% per week	*N* = 30 in 8wks, 13% per week or greater	End of recruitment
	Participation rates	Participation rate <5%	Participation rate 5–15%	Participation rate 15–25%	Participation rate 25% or greater	6 months post-intervention
	Retention rates	Attrition >75%	Attrition 50–75%	Attrition 30 − 50%	Attrition <30%	6 months post-intervention
	End interviews	N/A	Major suggestions to improve recruitment processes	Minor suggestions to improve recruitment processes	No suggestions to improve expressed	1 month post-intervention (week 26)
Identify number of eligible participants, participant rates and retention rates	Number identified by HCPs	<50 identified	50–100 identified	100–128 identified	>128 potentially eligible identified	End of recruitment
	Number expressing interest	<30 express interest	30–40 express interest	40–60 express interest	>60 express interest	End of recruitment
	Number providing consent	<15 provide consent	15–25 provide consent	25–30 provide consent	30 provide consent	End of recruitment post-intervention, 3 and 6 months post-intervention
	Number lost to follow up	Attrition >75%	Attrition 50–75%	Attrition 30–50%	Attrition <30%	

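### Table 1 gives Stop and Continue-with-modification the same therapist-adherence cut-off (<50%), so that row cannot separate the two decisions

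*Protocol article*

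**What the plan says.** The section Outcome measures and endpoints makes Table 1 the home of the progression rules: "A summary of the main feasibility outcomes, success criteria and timing is shown in Table 1". The table has four ordered decision columns: Stop, "Continue, modify protocol", continue unmodified with close monitoring, and continue unmodified.

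Two rows deal with adherence, both assessed at the end of the intervention.

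- **Intervention components, method Therapist adherence.** The Stop cell and the modify cell both read "Adherence <50"%. The monitor cell reads "Adherence 50–75"% and the last cell is >75%.
- **Intervention adherence.** The methods cell reads "Therapist self-rated adherence Video-rated adherence". The Stop cell reads "Adherence <25"%, the modify cell "Adherence 25–50"%, and the upper two cells are again 50–75% and >75%.

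The attendance (Compliance) row sets Stop at a mean below 10 sessions, modify below 14, monitor at "Mean attendance 14 sessions", and continue at 14+.

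**The concern.** A progression table works only if each possible result leads to one decision. In the Therapist adherence line, two of the four columns have the same condition, and one of them is Stop. A low result then leaves the team free to choose between stopping and continuing with changes once the data are known, which is what thresholds set in advance are meant to prevent.

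The point is not peripheral. The article states that feasibility of the design and the intervention is its main interest. Aims and objectives lists the testing of components and the measurement of adherence, and Nested process evaluation puts treatment fidelity first among its aims. The criterion is also stated and not merely left out, so it is not something that an analysis plan would be expected to fill in.

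**Working it through.** No sample-size or error-rate formula is involved. The check maps each adherence value to the decision columns of the two rows.

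**Inputs (Table 1).** Write x for adherence in per cent.

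| Decision | Intervention components: Therapist adherence | Intervention adherence: self-rated and video-rated |
|---|---|---|
| Stop | x < 50 | x < 25 |
| Modify | x < 50 | 25 to 50 |
| Monitor | 50 to 75 | 50 to 75 |
| Continue | x > 75 | x > 75 |

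**Step 1: within the components row.** The set meeting Stop is {x < 50} and the set meeting Modify is {x < 50}, so they are identical. Of the 50 whole-number values from 0 to 49, all 50 meet both. If Stop is applied first, Modify is empty. If Modify is applied first, Stop is empty. Either way the row has three working bands, not four.

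**Step 2: within the adherence row.** No value meets both Stop and Modify. The only overlap at the lower end is exactly 50%, which lies in both 25–50% and 50–75%. That is a minor boundary matter.

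**Step 3: between the rows.** This step is meaningful only if the two rows score the same or overlapping measures.

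| x | Components row | Adherence row |
|---|---|---|
| 10 | Stop and Modify | Stop |
| 24 | Stop and Modify | Stop |
| 25 | Stop and Modify | Modify |
| 40 | Stop and Modify | Modify |
| 49 | Stop and Modify | Modify |
| 50 | Monitor | Modify and Monitor |
| 60 | Monitor | Monitor |
| 76 | Continue | Continue |

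The rows agree above 50%. Below that, a precedence rule alone would not remove the disagreement. With Stop first, the components row says Stop for 25 to <50% where the adherence row says Modify. With Modify first, it says Modify for 0 to <25% where the adherence row says Stop. Each choice leaves a clash 25 percentage points wide.

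**Step 4: is this just the table's style?** Other rows also use open-ended cut-offs in the first two columns: attendance <10 then <14, and screening <50 then <100. Their two numbers differ, so reading left to right gives a modify band of 10 to <14 sessions or 50 to <100 subjects. With two equal numbers, no reading order yields a band.

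**Step 5: could it be a text-extraction fault?** The row has all four criterion cells and its timing cell, and the upper two bands stand in their proper columns. A dropped or shifted cell is unlikely.

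**Step 6: attendance.** The monitor band is the single value 14. With 20 participants in the intervention arm, an unrounded mean of exactly 14 needs a total of exactly 14 × 20 = 280 attended sessions. If 14+ means 14 or more, that value also lies in the continue band.

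**The case against.** A reader might infer that the table sends one and the same fidelity result to opposite decisions in two rows. The documents do not establish this. The rows stand under different outcomes and name different methods, and Aims and objectives mentions testing components and measuring adherence as separate items. Two different measures may properly have different cut-offs. Shared timing and identical upper bands make overlap plausible, but the article defines neither measure. Nor is 'opposite' quite the word: Stop and Modify are adjacent columns, and neither allows the trial to go on unchanged.

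A reader might also infer that pre-specification of treatment fidelity is lost altogether. That goes too far. The Intervention adherence row carries the self-rated and video-rated measures in four ordered bands that touch only at shared endpoints. Intervention components has a second criterion as well, the end interviews. Nothing in Table 1 makes one row decisive for progression.

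On attendance, 14 beside 14+ can fairly be read as 14 against more than 14. The monitor band can then be reached, for example if the mean is reported to the nearest whole session, and shared endpoints occur elsewhere in the table. So this is a matter of tidiness only.

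None of this touches the duplicated cut-off. It stands in the current text, and nothing in the article resolves it.

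**Conclusion.** The point holds for the Therapist adherence line of Intervention components. Stop and Modify share one condition, so every value from 0% to just under 50% returns both decisions, and the row cannot tell stopping from continuing with modification. This rests on the printed cells alone.

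The disagreement with the Intervention adherence row is conditional on the two rows scoring the same or overlapping measures. If they do, the rows differ throughout the range below 50% and agree above it. If they do not, only the within-row fault remains.

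The neighbouring row's pattern suggests a slip in one cell, but the article does not say which cut-off was meant. The consequence is confined to one feasibility progression criterion. Sample size, randomisation and the clinical outcome analysis do not depend on it, and no interim analysis is planned that could use it.

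**What to change.** Before fidelity data are reviewed:

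1. Give the Stop and Modify cells of the Therapist adherence line distinct, mutually exclusive cut-points. The adjacent row's <25% for Stop and 25 to <50% for Modify is the evident candidate, but the sponsor should confirm what was intended.
2. State whether Therapist adherence and the self-rated and video-rated adherence are different measures. If they are, define each and keep both rows. If they are not, merge the rows. The components row should not be deleted on the assumption that it is a duplicate.
3. As a minor tidy-up, give the attendance 'monitor closely' column a range that does not overlap the continue column.

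The cost is the correction of a few table cells and a sentence of definition, with no change to design, data collection or analysis. The correction should be dated. If any adherence ratings have already been seen, it should say so, because new cut-points would then no longer be fully pre-specified.
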